##### Phenotypic and GSEM analyses

Case-case GWAS will explicitly compare ED cases (e.g., AN vs. BN; AN vs. BED etc.). Genomic structural equational modelling (GSEM) [51] will be applied to the GWAS summary statistics to identify common factors across EDs and between ED symptoms.

##### SNP-Heritability

We will estimate SNP-h^2^ with Genome-wide Complex Trait Analysis (GCTA) [52] based on individual genotypes to maximize accuracy. Covariate-adjusted LDSC [53] will be used to calculate partitioned SNP-h^2^ within homogenous and admixed populations using the best available population references for building LD scores (e.g., the latest high coverage 1000G whole genome sequencing [WGS] data) [47]. For discrete traits, GCTA and LDSC require an assumed lifetime population prevalence (K), and we will model a range of values to explore sensitivity.

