### Participants

EDGI2 will recruit 20,000 participants from the United States (US), Mexico (MX), Australia (AU), New Zealand (NZ), Sweden (SE), and Denmark (DK); within this recruitment target we will enroll ~ 3000 individuals with longstanding and/or severe AN. Effort will be made to enroll individuals who have been less frequently studied including those with varying body sizes and males. The minimum adult age for inclusion will vary by country: 16 in NZ and SE; 18 in US, AU, and MX; and 21 in Puerto Rico, with no upper age limit. Child case participants will be included for MX (15–17 years of age) and must have parent/guardian consent to participate. DK participants will all be born in DK between 1981 and 2008.

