#### Control definitions

In the US, MX, and SE, controls will be selected based on the absence of lifetime ED symptoms as determined via the ED100K.v4 [2]. Controls must have a minimum lifetime adult BMI ≥ 18.55 and maximum lifetime BMI < 30 and no history of binge eating, compensatory behaviors, use of glucagon-like peptide-1 (GLP-1) receptor agonists, or atypical AN. They also cannot report a history of an ED in any first-degree relatives. For AU and NZ, controls will be selected from healthy donor samples in previously collected cohorts. In DK, control inclusion criteria will be the absence of lifetime AN, BN, or other ED diagnosis based on ICD-10 codes.

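### SNP-heritability: varying only the assumed prevalence K does not show the upward bias in estimates that rest mainly on symptom-screened US, MX and SE controls

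*Protocol article*

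**What the plan says.** The SNP-Heritability section plans GCTA "based on individual genotypes to maximize accuracy" and covariate-adjusted LDSC. For discrete traits it names one population quantity and one sensitivity analysis: "GCTA and LDSC require an assumed lifetime population prevalence (K), and we will model a range of values to explore sensitivity". It names no quantity for how controls were selected.

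The Control definitions section sets three different rules:

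- **US, MX, SE:** "In the US, MX, and SE, controls will be selected based on the absence of lifetime ED symptoms as determined via the ED100K.v4". In addition, "Controls must have a minimum lifetime adult BMI ≥ 18.55 and maximum lifetime BMI < 30 and no history of binge eating, compensatory behaviors", no GLP-1 receptor agonist use and no atypical AN. On family history: "They also cannot report a history of an ED in any first-degree relatives".
- **AU, NZ:** healthy donors from existing cohorts. ED screening of these donors is not stated.
- **DK:** "In DK, control inclusion criteria will be the absence of lifetime AN, BN, or other ED diagnosis", based on ICD-10 codes.

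Under Recruitment, only US, MX and SE recruit new controls. Under Analyses, DK, SE and NZ Māori/Pasifika raw data stay at their sites, so individual-level estimates there are local. On the case side, the Participants section states that "we will enroll ~ 3000 individuals with longstanding and/or severe AN".

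**The concern.** A conversion that uses K alone has one threshold. Cases are everyone above it and controls are everyone below it. A symptom-free rule also removes people who never met criteria but sit in the upper part of the non-case liability distribution. Excluding people with an affected first-degree relative selects on familial liability as well. Cases and controls then lie further apart than the formula assumes, and the surplus is read as heritability.

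Varying K moves the assumed case threshold but leaves the assumption about controls untouched. A reader could take the K-range as covering the main uncertainty when the true value lies below it. SE and DK estimates passed through the same conversion could also differ because of control definition alone.

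**Working it through.** **Nothing to reproduce.** The article gives no SNP-h², no K and no share of people failing the symptom screen. K, the screening fraction q, the true h² and all correlations below are assumptions, shown as ranges.

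**Formula.** Let t be the case threshold, z the normal density at t, t_q the threshold that cuts off the top share q, and φ the normal density.

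- Mean liability of cases: z/K.
- Mean of ordinary non-case controls: −z/(1−K).
- Mean of controls with the top share q removed: −φ(t_q)/(1−q).
- Inflation of the one-threshold estimate: [(z/K + φ(t_q)/(1−q)) / (z/K + z/(1−K))]². It does not depend on the case fraction in the sample.

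**Worked case, K = 1%, q = 20%.** z = 0.02665, so the case mean is 2.665 and the ordinary control mean is −0.027, a gap of 2.692. The screened control mean is −0.2800/0.80 = −0.350, a gap of 3.015. Inflation = (3.015/2.692)² = 1.25.

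**Range over K = 0.5% to 5%.** For correlations below 1, the screen acts on a symptom score correlated with liability to the disorder analysed.

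| Share removed | Correlation 0.3 | 0.5 | 0.7 | 1 |
|---|---|---|---|---|
| 10% | 1.04 | 1.06 | 1.07–1.09 | 1.08–1.13 |
| 20% | 1.07 | 1.12 | 1.16–1.17 | 1.23–1.26 |
| 30% | 1.10–1.11 | 1.17–1.18 | 1.24–1.26 | 1.36–1.40 |

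**Simulation check** (K = 5%, true h² = 0.20, correlation 1). Ordinary controls return 0.202 (SE 0.004). With q = 20% the result is 0.243 (SE 0.003; formula 0.247). With q = 30% it is 0.281 (SE 0.005; formula 0.278).

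**Does varying K show it?** True K = 1%, true h² = 0.15, correlation 1:

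| Assumed K | Ordinary controls | q = 10% | q = 20% | q = 30% |
|---|---|---|---|---|
| 0.5% | 0.129 | 0.145 | 0.161 | 0.178 |
| 1% | 0.150 | 0.169 | 0.188 | 0.207 |
| 2% | 0.178 | 0.201 | 0.223 | 0.246 |

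Screening lifts the whole curve by the same factor at every assumed K. Over this K-range, 0.15 falls below every value at q = 20% or 30%. At q = 10% it is still covered, but off-centre.

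**Dilution, K = 1%, correlation 1, q = 10–30%.**

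- Half the controls screened: 1.06–1.18.
- One tenth screened: 1.01–1.04.
- Only the 1,300 new controls among about 730,000 (0.18%): at most 1.0006.

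**BMI limits, K = 1%.** Assume the upper limit removes 20–40% of people and the lower limit 3%. With a liability–BMI correlation of −0.1 to −0.3 and symptom–liability correlation 1, the net factor is 1.02–1.11 at q = 10% and 1.16–1.24 at q = 20%. With +0.1 to +0.3 it is 1.14–1.22 and 1.27–1.32. The BMI limits alone (q = 1%, no extra symptom screening) give 0.88–0.98 for the negative correlations. At the weak end of the first table, where the symptom screen adds only about 4%, they could therefore cancel it. The family-history exclusion was not modelled; it should push upward.

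**The case against.** The strongest reply is that the conversion formula is inferred and that an article may leave such detail to the full plan. That stands as a limit on certainty. But the section does commit to K as the input and to varying K as the sensitivity analysis, and neither reflects the control rules.

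Several stronger readings are tempting, and the documents do not support them:

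- **That SNP-h² for every ED is overstated.** Which controls enter GCTA is not stated. AU/NZ donors are of unstated number and screening and may be pooled with US and MX. DK controls need only lack a diagnosis. In LDSC on the full meta-analysis the new controls count for almost nothing, and screening of the external controls is not stated.
- **That the inflation is 23–55%.** This needs 20–40% removed and a screen that cuts liability perfectly. Binge eating or compensatory behaviours need not track liability to ARFID or restricting AN closely.
- **That recruiting severe AN adds to the bias.** The article says only that DNA from these cases may reflect higher genetic burden. No effect has been computed. The 3,000 or so compare with about 47,000 AN cases in the meta-analysis.
- **That estimates cannot be compared with published ones.** This depends on how those studies screened controls, which is not shown.
- **That one corrected bound, set from the share of would-be controls failing the ED100K.v4, would solve it.** They are volunteers already filtered by a prescreen. At 30% removed, dividing by the perfect-correlation factor leaves h² about 9–10% too low if the correlation is 0.7, and about 14–15% too low if it is 0.5.

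The article also offers the K-range only to explore sensitivity, not as full uncertainty. That softens the point but does not remove it, since no other sensitivity analysis is named for the conversion.

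**Conclusion.** The concern holds in limited form. Where estimates rest mainly on US, MX or SE controls, a K-only conversion is biased upward and varying K cannot reveal it. The overstatement is about 4–13% if screening removes 10% of the population and about 10–40% if it removes 30%, for K between 0.5% and 5% and symptom–liability correlations from 0.3 to 1. It shrinks with pooling of unscreened controls, and for AN the BMI limits may offset part of it if liability to AN correlates negatively with BMI. From the 1,300 new controls it is negligible in the full meta-analysis, and it does not apply in this way to DK. The conclusion rests on the liability-threshold model and on the inferred one-threshold conversion. No GWAS locus is affected; what changes is how far the reported SNP-h² range can be relied on.

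**What to change.** In the SNP-Heritability section:

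1. State which controls enter each GCTA and cohort-level estimate.
2. Keep the standard conversion. For estimates with symptom-screened controls, add a conversion with separate case and control thresholds.
3. Vary the control-screening fraction and an imperfect symptom–liability correlation over a stated range, jointly with K. Do not take a single bound from volunteer screeners.
4. Report DK separately from the screened-control sites. DK covers AN and BN only, so it offers no contrast for BED or ARFID.
5. Repeat the AN estimate without the targeted severe cases, as a sensitivity check.

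The cost is a little extra analysis on data already planned, a wider reported range and somewhat lower h² values. No new recruitment or genotyping is needed.

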##### Genetic Correlations

We will estimate *r*_*g*_ between ED traits and other psychiatric, metabolic, and anthropometric traits using LDSC and LAVA [54]. Since LDSC is limited to within-ancestry comparisons, we will apply POPCORN [55] and GCTA bivariate GREML [56] for trans-ancestry correlation analyses.

##### Polygenic Risk Score

PRS aggregate risk alleles across the genome, weighted for effect size, to provide an estimate of an individual’s risk for a disorder or trait. We will compare two methods, the classical *P*-value thresholding method and SBayesRC [57], and implement appropriate cross-population approaches, for example PRS-CSx [58]. Exclusion criteria for *P*-value thresholding include uncommon SNPs (MAF < 0.01), low quality variants (imputation INFO score < 0.7), indels, strand ambiguous SNPs, and SNPs within the highly variable extended MHC region (chr6:25–34 Mb). As standard, SNPs will be LD pruned and clumped. *P*-value thresholds are predefined (0.001, 0.01, 0.05, 0.1, 0.5). We will use SBayesRC to calculate PRS while modeling LD.

##### Rare CNV Analyses

To explore rare CNVs, we will use a clustering approach. CNVs will be called with validated complementary calling algorithms, iPattern [59], PennCNV [60], and QuantiSNP [61] in EnsembleCNV [62], which enables highly accurate CNV calling from SNP array data. Stringent QC include: exclusion of LogRDev Z > 2, BalleleDev Z > 2, or fragmented CNVs; samples with < 98% call rate, autosomal heterozygosity greater than five, unresolvable sex mismatch, unreliable calls (low-confidence score, < 10 probes, or only called by a single algorithm) will be excluded; and spurious calls will be filtered with QC CNV metrics, small CNVs, or CNVs where > 50% overlaps low confidence genomic regions, or hypervariable regions in white blood cells will also be excluded. Adjacent CNVs overlapping by > 75% will be annealed. Additional QC will be applied as necessary to DK bloodspots [63] and analysis may be limited to CNVs relevant to neuropsychiatric disorders (*N* = 53) [64–66]. Batch-wise Firth logistic regression (including covariates) will test CNV burden in cases and controls, followed by standardization of results with Stouffer’s signed Z-value meta-analysis. Rare CNV burden parameters include count, total and average length (kilobases [kb]), number of protein coding genes implicated, and total overlapped evolutionarily constrained bases [67]. Additionally, novel CNVs will be detected with breakpoint analyses via Firth’s logistic regression.

##### Bioinformatics analysis and integration

Bioinformatic analysis and integration will leverage existing data and code from previous PGC investigations and publicly available sources. As in previous ED GWAS (ANGI [2], EDGI [1]), initial gene enrichment analyses will be performed in the web browser-based application FUMA [68] as a starting point, due to its easily sharable graphical output, and then address seven major domains of bioinformatics integration. Basic SNP annotation includes evolutionary constraint scores for primates, mammals, and vertebrates, functional annotation of gene components, and enrichment for all major psychiatric GWAS results. Statistical fine mapping will be performed to identify putatively causal SNPs at each locus, using FINEMAP [69] and SuSie [70]. Common indel imputation will be performed with TOPMed and expanded 1000G imputation reference (as allowable) to enable investigation of putatively informative indels at locations such as gene regulatory regions. We will perform comprehensive gene annotation followed by enrichment analysis with stratified LDSC to address the need for contextual interpretation of GWAS loci. This will include annotating risk loci, in addition to the basic SNP annotations, whole exome sequencing (WES), and snRNA-seq for differential gene expression in psychiatric disorders, Mendelian inheritance patterns, and brain cell-type specific gene expression. Integration of GWAS data with functional genomics will be performed with available annotation databases of both bulk tissue and cell specific regulatory elements, chromatin regions, interaction regions, splicing and quantitative trait loci (QTL). For specific ED risk loci, we will emulate experimental evaluation of GWAS loci currently being undertaken for other psychiatric disorders, including the use of massively parallel reporter assays (MPRA), and dCas9 epigenome editing to experimentally validate functional consequences of risk loci.

##### Power

We have sufficient power (> 80%) for case–control GWAS. BN, BED, and ARFID, specifically, will have power to detect common variants (MAF > 5%) with modest effect sizes (ORs: ARFID > 1.27; BN > 1.22; BED > 1.17), and low-frequency variants (MAF > 1%) with relatively large effect sizes (odds ratios [ORs] > 1.68, 1.52, and 1.41, respectively). From ANGI and EDGI, AN GWAS already has sufficient power for detection of common variants, which EDGI2 will improve. This will be the first ED GWAS with sufficient power for case-case analyses. The largest case-case analysis will be able to detect common low-effect variants and low-frequency moderate-effect variants (OR > 1.18 and OR > 1.4, respectively), while the smallest case-case analysis will be able to detect common moderate effect variants, and low frequency large effect variants (OR > 1.35 and OR > 1.8). Analyses for heritability, *r*_*g*_, and PRS all have sufficient power.

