**Methods:**

A total of 20,000 new participants (18,700 cases and 1,300 controls) will be ascertained from the United States (US), Mexico (MX), Australia (AU), Aotearoa New Zealand (NZ), Sweden (SE), and Denmark (DK). Comprehensive phenotyping and genotyping will be performed for participants in US, MX, AU, NZ, and SE using the EDGI2 questionnaire battery and participant saliva samples. In DK, case identification and genotyping will be through the National Patient Register and bloodspots archived near birth. Case–control and case-case genome-wide association studies will be conducted within EDGI2 and enhanced via meta-analysis with external data from the Eating Disorders Working Group of the Psychiatric Genomics Consortium (PGC-ED). Additional analyses will explore genetic correlations between eating disorders (EDs) and other psychiatric and metabolic traits, calculate polygenic risk scores (PRS), and leverage functional biology to evaluate clinical outcomes. Moreover, analyzing PRS for patient stratification and linking identified risk loci to clinically relevant phenotypes highlight the potential of EDGI2 for clinical translation.

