##### GWAS

GWAS will be performed by ancestry groups for each primary ED diagnosis, component behaviors, and dimensional traits captured through the EDGI2 battery. Binary and continuous GWAS will include correction for relevant covariates including sex, age, and genotype-derived principal components (PC) to correct for population stratification. The number of appropriate PCs will be determined using PCAiR.

For each ED, ancestry-specific EDGI2 GWAS will be meta-analyzed using MR-MEGA [49]. Where possible EDGI2 cohorts will be meta-analyzed with PGC-ED GWAS summary statistics, and any other publicly available ED GWAS summary statistics. In total, meta-analyses are expected to yield ~ 80,000 cases and ~ 730,000 controls (case-specific breakdown: AN≈47,000; BN≈16,000; BED≈10,000, ARFID≈6,500). By the time of analysis, additional cases may be contributed from independent international sites. Significant GWAS loci will be identified through standard per-GWAS Bonferroni correction and a conditional false discovery rate (FDR) approach across GWAS to identify shared loci [50].

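### The case–control power figures match pooled case counts sharing about 100,000 or more controls, but external controls cannot serve EDGI2's own cases, so ARFID and BED power depends on unstated control numbers

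*Protocol article*

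**What the plan says.** All references are to the protocol article.

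- **Power (Aim 2a):** "We have sufficient power (> 80%) for case–control GWAS". For common variants (MAF above 5%) it gives "modest effect sizes (ORs: ARFID > 1.27; BN > 1.22; BED > 1.17", and for low-frequency variants (MAF above 1%) "relatively large effect sizes (odds ratios [ORs] > 1.68, 1.52, and 1.41, respectively". It gives no control count.
- **GWAS:** "In total, meta-analyses are expected to yield ~ 80,000 cases and ~ 730,000 controls", with cases by disorder of "AN≈47,000; BN≈16,000; BED≈10,000, ARFID≈6,500". On the significance level: "Significant GWAS loci will be identified through standard per-GWAS Bonferroni correction"; no number is given.
- **Abstract, Methods:** "A total of 20,000 new participants (18,700 cases and 1,300 controls) will be ascertained from the United States (US" and five other countries.
- **Control definitions and Recruitment:** "In the US, MX, and SE, controls will be selected based on the absence of lifetime ED symptoms as determined via the ED100K.v4". Australia and New Zealand recruit no new controls and use donors from earlier cohorts. Denmark draws controls from its register. Neither the donor nor the Danish control count is given.
- **Case definitions:** Denmark contributes no ARFID or BED cases.
- **Analyses, Genotyping/QC and GWAS:** disorders are analysed separately and GWAS are run by ancestry group. Denmark, Sweden and the Māori/Pasifika part of New Zealand return summary statistics only. EDGI2 results are then meta-analysed with external summary statistics.

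**The concern.** In a meta-analysis each cohort contributes information in proportion to 1/(1/cases + 1/controls), using only controls analysed with those cases. A large control group inside an external GWAS sharpens that GWAS and lends nothing to cases in another. EDGI2 recruits about 14 cases per new control (18,700/1,300 = 14.4), so a pooled calculation can credit its new cases with information that the planned analysis does not deliver.

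ARFID and BED are the most exposed, because the Danish register controls cannot help them. If few loci emerge for these disorders, the result will be read against the stated power. If that power rests on controls the cases do not have, a lack of information could be taken for a lack of effect.

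**Working it through.** **Inputs.** Cases by disorder and the control total come from GWAS; odds ratios and MAFs from Power (Aim 2a); 18,700 and 1,300 from the Abstract. Assumed: two-sided alpha 5e-8 (z = 5.451), an allelic test with two alleles per person, control allele frequency equal to the MAF, and the case frequency p1 derived from the OR.

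**Step 1: which denominators give the printed figures?** With d = p1 − p0, s0 the pooled (null) standard error and s1 the unpooled one, power = Φ((d − z·s0)/s1).

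ARFID, MAF 5%, OR 1.27, 6,500 cases v 730,000 controls: p1 = 0.06265, d = 0.01265, s0 = 0.001922, s1 = 0.002133. Power = Φ((0.01265 − 5.451 × 0.001922)/0.002133) = Φ(1.02) = 85%.

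| Denominators | Minimum OR at 80% power, MAF 5% / 1% | Printed OR | Power at printed OR |
|---|---|---|---|
| ARFID 6,500 v 730,000 | 1.26 / 1.58 | 1.27 / 1.68 | 85% / 95% |
| BN 16,000 v 730,000 | 1.17 / 1.37 | 1.22 / 1.52 | over 99% / over 99% |
| BED 10,000 v 730,000 | 1.21 / 1.47 | 1.17 / 1.41 | 39% / 58% |
| All 80,000 v 730,000 | 1.08 / 1.17 | none | – |

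ARFID at 1.27 reaches 80% with about 103,000 controls. With the BN and BED odds ratios exchanged, power is 83% / 93% for BN and 86% / 92% for BED. The printed values therefore fit pooled per-disorder case counts with very many controls, but BN and BED do so only with labels exchanged. The case-case odds ratios point the same way. Pooled AN v BN gives 1.20 / 1.47 against a printed 1.18 / 1.4 for the largest comparison. Pooled BED v ARFID gives 1.36 / 1.88 against 1.35 / 1.8 for the smallest.

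**Step 2: effective cases under the planned analysis, ARFID.** Let x be EDGI2's own ARFID cases and C the controls analysed with them. Treating external controls as unlimited, effective cases E = (6,500 − x) + 1/(1/x + 1/C). For x = 3,250 and C = 1,300: 3,250 + 929 = 4,179.

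| EDGI2 share of 6,500 | C = 1,300 | C = 5,000 | C = 10,000 |
|---|---|---|---|
| 10% (650) | 6,283 | 6,425 | 6,460 |
| 23% (1,495) | 5,700 | 6,156 | 6,306 |
| 50% (3,250) | 4,179 | 5,220 | 5,703 |

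**Step 3: power at OR 1.27, MAF 5%.** Two strata: external cases v 728,700 controls (730,000 − 1,300), and x v C. Each stratum is weighted by w = 1/(1/cases + 1/controls). The combined variances are V0 = Σw²s0²/(Σw)² and V1 = Σw²s1²/(Σw)², and power = Φ((d − z√V0)/√V1).

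| EDGI2 share | C = 1,300 | C = 5,000 | C = 10,000 |
|---|---|---|---|
| 10% | 82% | 84% | 84% |
| 23% | 73% | 80% | 82% |
| 50% | 41% | 63% | 73% |

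A hand check, Φ(6.47·√(E/6,500) − 5.451), agrees to within about one point: E = 4,179 gives 40%. Power drops below 80% at a share of about 14% with 1,300 controls and about 24% with 5,000.

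**Step 4: sensitivity.** A log-OR Wald test starts at 87%. With 1,300 controls it gives 84%, 77% and 40% at shares of 10%, 20% and 50%, and the minimum detectable OR at a 50% share is 1.33. The low-frequency ARFID figure (OR 1.68, MAF 1%) has more slack: by the Step 3 formula a 23% share gives 89% with 1,300 controls and 93% with 5,000. If BED's common-variant figure is really 1.22, the Wald form gives 88%, falling to 78% and 37% at shares of 20% and 50% with 1,300 controls.

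Treating EDGI2 as a single cohort is favourable, since splitting by ancestry or site cannot raise the sum of 1/(1/cases + 1/controls).

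**The case against.** The strongest reply is that the article never says how power was computed, and that its control supply is wider than the 1,300.

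- A reader might infer that power was computed on 80,000 cases v 730,000 controls. The documents do not support this. Those are expected totals over all disorders, and they would give odds ratios of about 1.08 and 1.17, well below those printed.
- A reader might infer that all EDGI2 cases face only 1,300 controls, so that 18,700 cases carry the information of 1/(1/18,700 + 1/1,300) = 1,216, or 6.5%. No section plans that. Australia and New Zealand use donor cohorts, and Denmark has register controls for AN and BN.
- Raw data from the US, Mexico, Australia and most of New Zealand are held together and analysed by ancestry group, so donor controls could serve US or Mexican cases of similar ancestry. This stands, and is why C is varied up to 10,000.
- EDGI2's share of each disorder is not given. At a 10% share ARFID power stays above 80% even with 1,300 controls. BN at its printed 1.22 also has slack: in the Wald form it is still 80% at a 50% share with 1,300 controls.
- A condensed article may leave cohort-level inputs to the full protocol. That is fair, and their absence is not the point. The point is that the article asserts power at specific odds ratios which fit a pooled control group that its own analysis does not provide.

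**Conclusion.** The point holds in conditional form. The printed odds ratios match pooled per-disorder case counts against about 100,000 or more shared controls, whereas separate GWAS are analysed and then meta-analysed. ARFID has the least room: its common-variant power starts at about 85% and falls below 80% once roughly 14% of its cases are EDGI2's with 1,300 controls, or roughly 24% with 5,000. BED is exposed in the same way if its intended figure is 1.22.

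It would go too far to say that power is below 80%. The EDGI2 share and donor count are unstated, and alpha and the test form are assumptions, so the loss is a range.

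One inconsistency does not depend on the share. BED at 1.17 with 10,000 cases has only about 39% power even against 730,000 controls, and BN has more cases than BED yet a larger detectable OR. An alpha between 5e-9 and 5e-8 leaves that ordering unchanged.

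**What to change.** 1. Recompute the case–control figures in Power (Aim 2a) from the sum over analysed cohorts of 1/(1/cases + 1/controls), counting only controls analysed in the same GWAS as those cases. State alpha and the test form.
2. Restate the detectable odds ratios, or the power at the printed ones, for each disorder. Give the EDGI2 share of cases and the donor and register control counts used.
3. Print effective sample size beside the 80,000 and 730,000 totals in Aim 1 and GWAS.
4. Reconcile the BN and BED odds ratios with the case counts in GWAS.

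The cost is a recalculation and probably less favourable stated figures for ARFID and BED. It needs no new participants.

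### The detectable odds ratios for BN and BED run in the opposite order to their case counts, so either the odds ratios or the counts are mislabelled, or the BED figure cannot be met

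*Protocol article*

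**What the plan says.** The GWAS section (Analyses, Aim 2a) gives the expected meta-analysis size per disorder: "AN≈47,000; BN≈16,000; BED≈10,000, ARFID≈6,500". For controls it gives only an overall figure: "In total, meta-analyses are expected to yield ~ 80,000 cases and ~ 730,000 controls". On the threshold it says "Significant GWAS loci will be identified through standard per-GWAS Bonferroni correction" and gives no number.

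The Power section that follows states "We have sufficient power (> 80%) for case–control GWAS". For variants with MAF above 5% it describes "modest effect sizes (ORs: ARFID > 1.27; BN > 1.22; BED > 1.17". For MAF above 1% it gives "odds ratios [ORs] > 1.68, 1.52, and 1.41, respectively", which in the order of the preceding list means ARFID 1.68, BN 1.52 and BED 1.41.

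**The concern.** At the same alpha, allele frequency and controls, more cases mean a smaller detectable odds ratio. BN has 6,000 more expected cases than BED, yet BED is given the smaller odds ratio at both frequencies. ARFID, with the fewest cases, has the largest, as it should.

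Each disorder gets its own GWAS, and the Power section is the only place where the article states the sensitivity of the BN and BED scans. If the odds ratios carry the wrong labels, the BED scan is described as more sensitive than it will be. If the counts carry the wrong labels, the sample-size breakdown is wrong for two of the four disorders.

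**Working it through.** **Inputs from the article.** Cases: BN 16,000, BED 10,000, ARFID 6,500. Controls: about 730,000 in total. Odds ratios: ARFID 1.27/1.68, BN 1.22/1.52, BED 1.17/1.41 (MAF 5% / 1%). Target power: above 80%.

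**Assumptions.** Two-sided alpha 5e-8 (z = 5.451), since no GWAS alpha is given. All 730,000 controls serve each disorder, since no split is given; this is the favourable end of the range. MAF sits at the stated floors.

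**Formulas.** Allelic test with 2n alleles per group. Control frequency p0 = MAF; case frequency p1 = OR·p0 / (1 − p0 + OR·p0).
- Unpooled: power = Φ[(p1 − p0)/s1 − z], with s1² = p1(1 − p1)/(2·cases) + p0(1 − p0)/(2·controls).
- Pooled: power = Φ[((p1 − p0) − z·s0)/s1], with s0 computed from the pooled frequency.
- Log-OR: power = Φ[ln(OR)/s − z], with s² = 1/(2·cases·p1(1 − p1)) + 1/(2·controls·p0(1 − p0)).

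**Step 1. Reproduce a stated figure.** For ARFID with 6,500 cases, the odds ratio giving 80% power is 1.258-1.288 (MAF 5%) and 1.57-1.73 (MAF 1%) across the three formulas. The stated 1.27 and 1.68 lie inside, so these assumptions are consistent with the article's calculation.

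**Step 2. BED as printed, 10,000 cases.**
- OR 1.17, MAF 5%: p1 = 0.0585/1.0085 = 0.05801, difference 0.00801.
  - Unpooled: s1 = 0.001663, so 4.816 − 5.451 = −0.636 and power is 26%.
  - Pooled: s0 = 0.001553, so (0.008007 − 0.008467)/0.001663 = −0.277 and power is 39%.
  - Log-OR: 0.1570/0.03049 − 5.451 = −0.301 and power is 38%.
- OR 1.41, MAF 1%: p1 = 0.0141/1.0041 = 0.01404, difference 0.00404.
  - Unpooled: 4.835 − 5.451 = −0.616 and power is 27%.
  - Pooled: (0.004042 − 0.003872)/0.000836 = 0.204 and power is 58%.
  - Log-OR: 0.3436/0.06067 − 5.451 = 0.212 and power is 58%.

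A 1-df additive Wald calculation gives 26% in both cells.

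**Step 3. Can other inputs rescue BED?**
- Controls: unlimited controls give at most about 41% (OR 1.17) and 60% (OR 1.41). Four controls per case give 20% and 32%, and one per case 3% and 4% (pooled).
- Alpha (OR 1.17, MAF 5%, pooled): 1e-5 gives about 75%; 80% needs about 2e-5, some 400 times 5e-8.
- Allele frequency: at MAF 8%, OR 1.17 has 71% (unpooled), 81% (pooled) or 82% (log-OR).

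**Step 4. Match the pairs to the counts** (80% power, 730,000 controls, three formulas):

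| Cases | OR at MAF 5% | OR at MAF 1% | Stated pair that fits | Printed label of that pair |
|---|---|---|---|---|
| 16,000 | 1.165-1.177 | 1.36-1.43 | 1.17 / 1.41 | BED |
| 10,000 | 1.208-1.227 | 1.46-1.56 | 1.22 / 1.52 | BN |
| 6,500 | 1.258-1.288 | 1.57-1.73 | 1.27 / 1.68 | ARFID |

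BN as printed (16,000 cases, 1.22/1.52) has about 98% power or more in both cells.

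**Step 5. Does BN need a swap?** Not necessarily. With 16,000 BN cases, 24,000 controls give 1.219/1.504 (pooled) and 25,000 give 1.221/1.520 (unpooled), close to the printed BN pair.

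**Step 6. Do the case-case figures decide which item is wrong?** The smallest comparison, 10,000 versus 6,500 cases, gives 1.35/1.83 (pooled) against the stated 1.35/1.8. That supports the set of counts. Exchanging the BN and BED labels leaves a 10,000-versus-6,500 comparison in place, so it does not show which disorder owns the 10,000.

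**The case against.** The case on the other side has four parts.

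1. *It is tempting to infer that the BED scan really has 26-58% power.* The documents do not support this as a fact. If the counts are the exchanged item, BED has 16,000 cases and 1.17/1.41 is about right. The low power holds only if the printed counts are correct. This stands.

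2. *A reader might infer that a two-way swap is proven and that BN is undersold.* That requires all 730,000 controls for each disorder, whereas the article gives 730,000 in total. External data are added only where possible, and Denmark contributes no BED or ARFID cases (Case definitions), so control sets may differ. Step 5 shows that a BN control set of about 20,000-25,000 would explain the BN pair without a swap. This stands for BN. It does not help BED, where unlimited controls are not enough.

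3. *The shortfall applies at the MAF floors and at an assumed alpha.* This stands as a limit on size: above MAF 8% much of the common-variant range is adequately powered at OR 1.17. But the claim is worded for all MAF above 5%, and the ARFID pair fits at the floor, so the floor is the natural basis. An alpha that rescued BED would be far from the conventional genome-wide level.

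4. *No test, threshold or recruitment target uses these odds ratios, and an article may leave the power model to the full plan.* True, and it limits the consequence. The point is not a missing detail, however, but two printed sets of figures that conflict.

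Reading the low-frequency odds ratios in another order does not help. The order BN, BED, ARFID would give ARFID, with the fewest cases, the smallest value, and the common-variant figures are labelled explicitly.

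**Conclusion.** The order of the BN and BED odds ratios conflicts with the order of their case counts, and one of the two sections needs correcting. What is firm: 10,000 BED cases cannot give 80% power at OR 1.17 (MAF 5%) or OR 1.41 (MAF 1%) at alpha 5e-8 with any number of controls. If the counts are right, BED power at those floors is about 26-39% and 27-58% with 730,000 controls, and lower with fewer.

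What is likely but not shown: an exchange of labels, since all six stated values fall in the computed ranges once the BN and BED pairs are exchanged. Whether the odds ratios or the counts are the mislabelled item, and whether BN's figure reflects a smaller control set, cannot be settled from the article. Nor does it plan to read a null BED locus as evidence of no effect, so that consequence is a risk for readers rather than a stated intention.

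**What to change.** Reconcile the GWAS and Power sections against the original power calculation.

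- If the case counts stand, restate BED as about OR > 1.22 (MAF 5%) and > 1.52 (MAF 1%). Restate BN as about OR > 1.17 and > 1.41 if the full control set applies; otherwise keep the BN pair and give the control number behind it.
- If the odds ratios stand, exchange the BN and BED case counts.

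The restated pairs are approximate: with 730,000 controls, BED at 1.22/1.52 has 74-88% / 68-96% power and BN at 1.17/1.41 has 73-85% / 74-95%, depending on the formula. A short note of the alpha and controls per disorder beside the odds ratios would let a reader check them.

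The cost is wording only. No design element or analysis changes; the BED figure becomes less favourable if the counts stand.
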